
#### 2.2.2. Sample Size

With reference to an exploratory pilot study in which a sample size of 12 per group was recommended [26], the sample size of this trial was 24 participants (12 per group). This is the first randomized controlled trial to investigate the efficacy, safety, and economic evaluation of WBGCT for UACS-induced chronic cough [18]. Considering a 20% dropout rate, 30 participants (15 per group) will be recruited.

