Descriptive statistics for each group regarding demographic characteristics and baseline data will be presented. Continuous variables will be expressed as means and confidence intervals, and an independent *t*-test or Wilcoxon rank-sum test will be performed depending on their normality. Categorical variables are expressed as frequencies and percentages, and χ2 test or Fisher’s exact test will be conducted. The primary outcome measures will be analyzed using the mixed effect model repeated measure (MMRM), setting each group and visit as a fixed effect and participants as a random effect. If necessary, the fixed effects will include variables with significant differences in demographic characteristics or variables that can affect chronic cough. Analysis of the primary outcome measures are expressed as mean and 95% confidence interval (CI). Among the secondary outcome measures, CSS scores for 4 weeks against baseline and cough VAS, NDS, LCQ-K, and QCSCS scores will be analyzed using the same methods as the primary outcome measure. Depending on normality, Student’s paired *t*-test or Wilcoxon signed-rank test will be used to analyze differences in scores before and after treatment. The IMOS and IMPSS scores at 2- and 4-week intervals will be analyzed using Fisher’s exact test. Repeated-measures analysis of variance (RM ANOVA) will be used to compare the differences in the changes in CSS score trends between the groups, and Dunnett’s procedure for multiple comparison correction will be used. When performing the Student’s paired *t*-test, Wilcoxon signed-rank test, or RM ANOVA, a missing data will be substituted with Last Observation Carried Forward (LOCF) or Multiple Imputation (MI).

A safety evaluation will be conducted on participants who receive Interventions at least once. The number of AEs between the groups will be compared using Fisher’s exact test. Differences in laboratory test variables before and after treatment will be analyzed using the Student’s paired *t*-test or Wilcoxon signed-rank test.

Economic evaluations will be performed from both social and limited social perspectives. In sensitivity analysis, the available variables will be analyzed using a one-way sensitivity analysis with a tornado diagram. If necessary, a probabilistic sensitivity analysis will be conducted using the distribution and representative values of the variables.

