In recent studies, the phytochemical and pharmacological mechanisms of the ingredients and active compounds in WBGCT have demonstrated potential effects that alleviate symptoms of UACS-induced chronic cough. Ephedrae Herba has been widely used for treating respiratory diseases such as asthma, allergic rhinitis, and common cold [21]. Ephedrine, a major active compound in Ephedrae Herba, has inhibitory effects on the infiltration of inflammatory cells into pulmonary tissues and the secretion of inflammatory mediators, depressing levels of tumor necrosis factor α (TNF-α) and interleukins. It is also a bronchodilator, stimulating β-adrenergic receptors in the lung [43,44,45]. Atractylodis Rhizoma has been used for treating dyspepsia, viral infection, and rheumatic diseases [46]. Among its compounds, atractylon has anti-inflammatory effects and alleviates influenza virus-induced pulmonary injury by decreasing pro-inflammatory cytokines (IL-1β, IL-6, and TNF-α) [47]. Gypsum Fibrosum, a mineral composed of calcium sulfate, has antipyretic and anti-inflammatory effects, which are achieved by reducing secretion of IL-4 in mice splenocytes [48,49]. Glycyrrhizin from Glycyrrhizae Radix et Rhizoma alleviates inflammation and oxidation by depressing the expression of cytokines and reactive oxygen species (ROS), inhibiting virus replication as well [50]. Gingerol, a phenolic compound of Zingiberis Rhizoma Recens, has antibacterial and antioxidative effects from oxidative damage [51]. These results support the therapeutic effects of WBGCT in USAC-induced chronic cough. The potential mechanisms of therapeutic effects on UACS-induced chronic cough ingredients of WBGCT are shown in Figure 2.

SCRT, the investigational medication in the active control group, is an herbal medication used for respiratory diseases, such as allergic rhinitis and the common cold [24,52], which has inhibitory effects on the infiltration of inflammatory cells in the airway [22]. Due to the therapeutic effects of SCRT on respiratory diseases, SCRT is selected for comparison with WBGCT. In this study, we also observe the clinical effects of SCRT on UACS-induced chronic cough, as no other studies on UACS using SCRT have been conducted.

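### Before-after significance tests of the efficacy scores are planned without being made subordinate to the between-arm analysis; they cannot compare the arms and should give way to descriptive change per arm

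*Protocol article*

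**What the plan says.** Section 2.9 of the protocol article gives three kinds of analysis for the efficacy scores.

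- **Between-arm model.** The primary outcome, the cough symptom score (CSS), is analysed with a mixed model for repeated measures, "setting each group and visit as a fixed effect and participants as a random effect". Week-4 CSS, cough VAS, NDS, LCQ-K and QCSCS "will be analyzed using the same methods as the primary outcome measure".
- **Before-after tests.** A paired t-test or, if normality fails, a "Wilcoxon signed-rank test will be used to analyze differences in scores before and after treatment". Laboratory before-after tests are planned separately, in the safety paragraph, so this sentence concerns the efficacy scores.
- **RM ANOVA.** This "will be used to compare the differences in the changes in CSS score trends between the groups".

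For the paired tests and the RM ANOVA, missing data are filled by last observation carried forward or multiple imputation. The section does not say whether the paired tests are run per arm or pooled, or whether they are descriptive.

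Section 4 adds that "we also observe the clinical effects of SCRT on UACS-induced chronic cough", and acknowledges that there is no placebo arm. Section 2.2.1 requires minimum daytime and nighttime cough scores for entry.

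**The concern.** The randomised question is WBGCT against SCRT, and a before-after p-value does not answer it on either reading. Pooled over arms, it says nothing about the contrast. Run by arm, it gives two p-values whose difference in significance is not evidence of a difference between products. A before-after change also contains natural improvement and, because entry needs a minimum score, possible regression to the mean. No placebo arm exists to separate these from a drug effect.

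At 12 to 15 participants per arm the between-arm interval will probably be wide. Section 5 nevertheless expects the study to support efficacy and clinical use. Significance tests that sit beside the randomised comparison, with no stated rank, offer a second route to an efficacy statement, and that route lacks the error control of the first.

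**Working it through.** **Inputs from the document.** Section 2.2.2: 12 evaluable per arm, 20% dropout, 15 recruited per arm. The stated inflation reproduces: 24 / (1 − 0.20) = 30, or 15 per arm. The 12 per group is a cited pilot-study recommendation, so there is no power calculation to reproduce.

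**Assumptions.** Section 2.9 gives no test level; two-sided 5% is taken, in line with its 95% intervals. The document gives no within-arm change and no SD of change, so dz (mean change divided by SD of change) is varied. Both arms have the same true dz, and the arms are independent.

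**One scale.** Let p be the power of the two-sided paired t-test in one arm, from the non-central t distribution with n − 1 degrees of freedom and non-centrality dz·√n. Then

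P(exactly one arm significant) = 2p(1 − p), which cannot exceed 50%.

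Example, n = 12 and dz = 0.6: p = 0.475, so 2 × 0.475 × 0.525 = 0.499.

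| dz | p, n=12 | discordant, n=12 | p, n=15 | discordant, n=15 |
|---|---|---|---|---|
| 0 | 0.05 | 9.5% | 0.05 | 9.5% |
| 0.2 | 0.097 | 18% | 0.112 | 20% |
| 0.4 | 0.245 | 37% | 0.303 | 42% |
| 0.6 | 0.475 | 50% | 0.580 | 49% |
| 0.75 | 0.658 | 45% | 0.771 | 35% |
| 1.0 | 0.883 | 21% | 0.949 | 10% |
| 1.2 | 0.965 | 7% | 0.991 | 2% |
| 1.5 | 0.997 | 0.6% | 1.000 | 0.1% |

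Discordance of 35% or more needs p between about 0.23 and 0.77, that is dz about 0.38-0.86 at n = 12 or 0.33-0.75 at n = 15. By symmetry half of the discordant trials favour WBGCT, so at most 25% of all trials. In simulation the signed-rank test behaved similarly (34-50% at n = 12 and 33-48% at n = 15 for dz 0.4-0.8), and a direct between-arm t-test on change stayed at about 5% for every dz.

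**Both arms significant.** This probability is p². At dz = 1.0 it is 0.883² = 78% (n = 12) and 0.949² = 90% (n = 15).

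**Five scales** (CSS, VAS, NDS, LCQ-K, QCSCS) at one time point, simulated with an assumed common correlation of 0.6. Chance that at least one scale is discordant:

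| dz | n=12 | n=15 |
|---|---|---|
| 0 | 32% | 31% |
| 0.4 | 77% | 83% |
| 0.6 | 92% | 90% |
| 0.75 | 87% | 75% |
| 1.0 | 52% | 29% |
| 1.2 | 22% | 7% |

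The like-for-like benchmark is at least one significant between-arm test over the same five scales, which is about 17% under identical products. The 5% for a single scale is not the right comparison here.

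**The case against.** The strongest reply is that the misuse is not in the document. A reader might infer that the trial plans to set one arm's p-value against the other's, or to conclude efficacy from the before-after tests. Section 2.9 says neither, and all five scales already have a between-arm model, with an RM ANOVA added for CSS. The section 4 sentence about observing SCRT is a descriptive aim, justified by the lack of earlier UACS studies of that formula, and announces no significance claim. Describing change within arms is ordinary in an exploratory trial. All of this stands, and it is why the discordance figures are conditional.

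A reader might also take 35-50% as the general rate of false contrasts. The document does not support that either. The range belongs to moderate within-arm changes, and outside it the single-scale rate falls well below 35%. A large change in both arms is plausible, since both products are active and entry is on a minimum score.

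What does not stand is that the tests are therefore harmless or only a detail for an unseen SAP. They are a stated choice with an imputation rule attached, and no reading makes them informative about WBGCT against SCRT. Where discordance is low because the change is large, both arms come out significant. That result invites the statement that both formulas work, which an uncontrolled comparison cannot support.

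**Conclusion.** The point holds in a limited form. The plan includes before-after significance tests of efficacy scores that do not compare the arms, cannot isolate a drug effect, and are not ranked below the between-arm analysis.

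If the tests are read by arm, identical products would appear to differ on one scale in up to half of trials when dz is moderate. With no change the single-scale rate is about twice the 5% of a between-arm test, and with very large changes it falls below 5%. Over five scales the rate exceeds the 17% benchmark at every dz examined except 1.2 with 15 per arm. These sizes rest on the assumed dz, the assumed correlation of 0.6, a two-sided 5% level and the arm-by-arm reading.

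Severity is minor. The trial is exploratory, and the primary between-arm analysis is not affected.

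**What to change.** In section 2.9:

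1. Drop the paired t-test and signed-rank test for the efficacy scores. The imputation rule may stay, because it also serves the RM ANOVA.
2. Add a group-by-visit term to the planned mixed model. As worded, the model has group and visit only. Its fitted mean is then μ + group effect + visit effect, the group effect cancels in a change from baseline, and both arms receive the same fitted change.
3. From that model report each arm's mean change at weeks 2 and 4 with 95% CI, labelled descriptive and without p-values. This still serves the aim of observing SCRT, and the section 4 plan to judge change against minimal clinically important differences.
4. State that any claim about WBGCT relative to SCRT rests only on the between-arm difference with its 95% CI.

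The cost is a change of wording and one extra model term. The report loses its within-arm p-values.

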## 2. Methods

### 2.1. Study Design

This is a randomized, double-blind, active-comparator-controlled, parallel, exploratory clinical trial to evaluate the efficacy, safety, and economic feasibility of WBGCT for UACS-induced chronic cough. Thirty participants will be recruited for this trial and randomly assigned to the WBGCT and control groups in a 1:1 allocation ratio. This trial consists of screening, 2-week treatment, and 2-week observation periods. The medications will be administered three times a day for 2 weeks. The detailed study design is summarized in Figure 1 and Table 1.

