#### 2.4.2. Secondary Outcome Measures

(1)Cough Visual Analog Scale (VAS).

The VAS evaluates cough severity and frequency. The score ranges from 0 to 10 (0 means “no cough” and 10 means “cough as severe as it could possibly be”) [31]. The VAS will be assessed on visits 2, 3, and 4.

(2)Nasal Discharge Score (NDS)

The NDS assesses the severity of two symptoms: nasal discharge (anterior nasal discharge score) and mucous globus sensation in the back of the throat (posterior nasal discharge score), ranging from 0 to 3 (0 = none; 1 = mild; 2 = moderate; 3 = severe) [6]. Since the symptoms of UACS include nasal symptoms, such as nasal discharge and rhinorrhea, symptoms related to nasal discharge will be assessed using the NDS in this trial [6]. The NDS will be evaluated on visits 2, 3, and 4.

(3)Questionnaire of Clinical Symptoms of Cough and Sputum (QCSCS)

The QCSCS is developed from the Clinical Asthma Measurement Scale in Oriental Medicine-V (CAMSOM-V) in the Traditional Korean Medicine Clinical Practice Guidelines for Antitussives and Expectorants, remodeled for cough and sputum [32,33]. The items for the QCSCS are as follows: (1) cough (frequency, intensity, and sensitivity), (2) sputum (frequency, volume, difficulty in coughing, appearance, and color), (3) activities of daily living, and (4) nighttime sleeping. Each item is measured using a 4-point scale, with a maximum total score of 40 points. The QCSCS will be assessed on visits 2, 3, and 4.

(4)Leicester Cough Questionnaire-Korean version (LCQ-K)

The LCQ-K evaluates the quality of life of patients with a cough and consists of 19 items divided into three parts: psychological, social, and physical aspects. Each item ranges from 1 to 7, with higher scores indicating a better quality of life. Previous studies have shown a correlation between the LCQ score and the severity of cough symptoms. The LCQ-K has been translated into Korean and verified for its validity and reliability [34,35]. The LCQ-K will be assessed on visits 2, 3, and 4.

(5)Integrative Medicine Outcome Scale (IMOS) & Integrative Medicine Patient Satisfaction Scale (IMPSS)

The IMOS evaluates symptom improvement. In this trial, the IMOS will be assessed by the investigators. The IMPSS is a rating scale used to assess treatment satisfaction of patients [36]. The scores on both scales range from 1 to 5. The IMOS and IMPSS will be evaluated on visits 3 and 4.

(6)5-level EuroQol 5-Dimensional Questionnaire (EQ-5D-5L)

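### Three supporting analyses in section 2.9 fit the data poorly: Fisher's exact test on ordered 1–5 ratings, LOCF as a permitted imputation, and a Dunnett correction that is empty with two arms

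*Protocol article*

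**What the plan says.** The trial has two arms: "Thirty participants will be recruited for this trial and randomly assigned to the WBGCT and control groups in a 1:1 allocation ratio" (section 2.1). Treatment lasts 2 weeks and is followed by 2 weeks of observation. CSS, the primary outcome, is recorded at all four visits (weeks −2, 0, 2 and 4; section 2.4.1 and Table 1).

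Section 2.9 analyses the primary outcome by MMRM, with group and visit as fixed effects and participant as a random effect. It names no interaction. Three supporting elements are in question:

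- **IMOS and IMPSS.** Section 2.4.2 says "The scores on both scales range from 1 to 5". Section 2.9 says "The IMOS and IMPSS scores at 2- and 4-week intervals will be analyzed using" Fisher's exact test.
- **Missing data.** For the paired t-test, the signed-rank test and RM ANOVA, "a missing data will be substituted with Last Observation Carried Forward (LOCF) or Multiple Imputation (MI"). The article gives no rule for choosing between the two.
- **CSS trends.** RM ANOVA is used "to compare the differences in the changes in CSS score trends between the groups, and Dunnett’s procedure for multiple comparison correction will be used".

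**The concern.** **Ordered ratings.** Fisher's exact test treats the five levels as unordered labels. If one arm tends towards better ratings, that shift is what a rank test is built to detect and what Fisher's test uses poorly. With so few participants the loss is not trivial.

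**LOCF.** A missing week-4 score would be replaced by the score at the end of treatment, although week 4 is off treatment. A missing week-2 score would be replaced by the baseline score, that is, by no change. The second case can arise within the full analysis set: section 2.9 drops participants who took no medication or gave no data after screening, and someone who has a week-0 CSS, starts treatment and is then lost need not be dropped. Within-arm change matters here because section 4 intends to judge effect against minimal clinically important differences, for want of a placebo arm, and to size the next trial from the observed effect.

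**Dunnett.** The procedure adjusts several comparisons against one control. Two arms give one between-group contrast, so there is nothing to adjust.

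**Working it through.** **Inputs.** From section 2.2.2: "the sample size of this trial was 24 participants (12 per group") evaluable, and "Considering a 20% dropout rate, 30 participants (15 per group) will be recruited". Check: 12 / (1 − 0.20) = 15 per arm, 30 in total, which agrees with the article. The 12 per arm follows a recommendation for pilot studies, so there is no power calculation to reproduce. The article gives no alpha in section 2.9; two-sided 0.05 is assumed from its 95% confidence intervals.

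**1. Fisher versus rank-sum on a 5-point scale.** Both tests were computed exactly on simulated 2×5 tables (2,000 replicates, simulation error at most √(0.5 × 0.5 / 2000) ≈ 1.1 points). The treated arm was a proportional-odds shift of the control arm. Assumed control distributions: A = 10/20/40/20/10% and B = 15/35/30/15/5%.

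| Control | n per arm | Odds ratio | Fisher | Wilcoxon | Loss (points) |
|---|---|---|---|---|---|
| A | 12 | 3 | 14.6% | 28.0% | 13.4 |
| A | 12 | 5 | 31.6% | 53.2% | 21.6 |
| A | 12 | 8 | 52.2% | 74.9% | 22.7 |
| A | 15 | 3 | 20.4% | 37.2% | 16.8 |
| A | 15 | 5 | 40.6% | 63.7% | 23.1 |
| A | 15 | 8 | 63.6% | 84.4% | 20.8 |
| B | 12 | 3 | 17.6% | 27.0% | 9.4 |
| B | 12 | 5 | 32.5% | 52.2% | 19.7 |
| B | 12 | 8 | 52.7% | 70.8% | 18.1 |
| B | 15 | 3 | 19.6% | 34.7% | 15.1 |
| B | 15 | 5 | 43.2% | 62.8% | 19.6 |
| B | 15 | 8 | 66.4% | 83.8% | 17.4 |

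With no true difference, both tests rejected in 4 to 5% of replicates. A separate run at 12 per arm gave about 20–23% versus 38–40% at odds ratio 4, and 37–40% versus 60–65% at odds ratio 6. Taken together, the loss is roughly 9 to 25 points.

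**2. LOCF.** Let d be the share missing at a visit. Assume that those missing have the same true mean change as the rest of their arm. Higher CSS is worse.

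- *Week 2, within arm.* Understatement of improvement = d × true improvement. With d = 0.20 (the planned dropout rate, all assumed to fall before week 2) and an assumed improvement of 2 points: 0.20 × 2 = 0.4 points.
- *Week 4, within arm.* Error = −d × g, where g is the true worsening from week 2 to week 4. With d = 0.20 and an assumed g = 1: −0.2 points, so the arm looks 0.2 points too good.
- *Week 4, between arms (WBGCT minus control).* Bias = −d_W × g_W + d_S × g_S. With 20% loss and g = 1 in both arms: −0.2 + 0.2 = 0. With 30% versus 10% loss and g = 2 versus 1: −0.6 + 0.1 = −0.5. With 10% versus 30% loss and g = 1 in both: −0.1 + 0.3 = +0.2. These two are the extremes of the values tried.

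**3. Dunnett.** With one contrast the critical value is the ordinary t value: 2.07 at 22 df (2 × 12 − 2) and 2.05 at 28 df (2 × 15 − 2). On simulated data the Dunnett and pooled t-test p values coincide: 0.322 and 0.322 at 12 per arm, 0.160 and 0.160 at 15 per arm. Comparing visits with baseline would raise the critical value to about 2.33–2.36 for two contrasts and 2.48–2.52 for three (correlation 0.5 assumed), but that tests time, whereas the sentence is about groups.

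**The case against.** These are supporting analyses in an exploratory trial with no power target, and the LOCF/MI sentence does not cover the MMRM. That stands, and it limits the weight of the point. The individual objections are these:

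- **Fisher is not wrong.** It holds its type I error, and it can detect non-monotone differences that a rank test may miss. The simulation assumes proportional odds, which favours the rank test, and at odds ratio 3 both tests are weak. All true. For improvement and satisfaction ratings a shift is nevertheless the pattern of interest, and the loss appears under both assumed distributions. A reader might infer that Fisher's test brings no benefit at all; that goes too far.
- **MI is already offered.** LOCF bias arises only if LOCF is chosen, and an analysis plan that is not shown may settle the choice. True, but the article lists LOCF as acceptable, and it suits neither week 2 nor week 4.
- **Dunnett does no harm.** Correct: an empty correction changes no p value. A visits-versus-baseline family is also possible and can be computed from a repeated-measures model with its own covariance, so that reading is not invalid; it is simply not what the sentence describes.
- **RM ANOVA has a role.** It is the only analysis the article assigns to CSS trends between groups. Deleting it and adding nothing would lose that comparison. This stands and shapes the fix.

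A reader might also infer that CSS will yield two conflicting sets of results, or that LOCF will create a false between-arm difference of 0.4 points. The documents support neither. Disagreement between MMRM and RM ANOVA is possible but not shown. A between-arm figure of 0.4 needs, for example, 30% versus 10% loss with a 2-point improvement in both arms ((0.30 − 0.10) × 2), and the article gives neither the timing of dropout nor any difference by arm.

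**Conclusion.** The point holds as a modest one about supporting analyses; the primary MMRM is untouched.

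- **IMOS and IMPSS:** the planned test is valid but inefficient, by roughly 9 to 25 percentage points of power. This rests on proportional odds, two assumed control distributions, odds ratios of 3 to 8 and two-sided 0.05.
- **LOCF:** within-arm change is biased whenever scores are missing and the true score moves, for example by 0.4 points at week 2 or 0.2 points at week 4 under the stated assumptions. The between-arm bias is zero when loss and change are equal in both arms and can take either sign otherwise, so no general figure can be given for it.
- **Dunnett:** empty and harmless for the comparison as written.

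**What to change.** Amend section 2.9 as follows:

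1. Compare IMOS and IMPSS between groups at weeks 2 and 4 by Wilcoxon rank-sum test (already used in section 2.9 for continuous variables) or a proportional-odds model. The small downside is less sensitivity to non-monotone differences.
2. Delete LOCF. Wherever a test needing complete data is kept, name multiple imputation in advance. Keep the imputation model small: imputing separately by arm may be unstable with 12 to 15 per arm, so a single model with arm and the CSS at other visits as predictors is an alternative.
3. Drop Dunnett's procedure and the RM ANOVA. Add a group-by-visit interaction to the MMRM explicitly, and report the interaction test and the group contrasts at weeks 2 and 4. The interaction must be written in, because the article names only group and visit; without it the planned trend comparison would disappear.

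The cost is a change of wording before unblinding. No data collection or sample size changes, and there is slightly less analysis to run.

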Previous studies have demonstrated the therapeutic effects of herbal medications in patients with UACS [13,14]. Wolbigachul-tang (WBGCT) is an herbal formula used to treat respiratory diseases such as asthma and allergic rhinitis [15,16]. It has been reported that WBGCT has antioxidant, anti-inflammatory, and antitussive effects on laryngeally-induced cough [17,18]. The hypothesized mechanism by which WBGCT has therapeutic effects against UACS-induced chronic cough is through the alleviation of upper airway inflammation. However, since the adverse effects of WBGCT including palpitation and insomnia have been reported [19], we will assess the safety of WBGCT, as well as its efficacy. In addition, to explore the possibility of using WBGCT with health insurance coverage, we will evaluate the economic feasibility of WBGCT by comparing it with Socheongryong-tang (SCRT), a health insurance-covered herbal formula used for respiratory symptoms. SCRT has been used for respiratory diseases, such as allergic rhinitis, asthma, and bronchitis [20,21], and has anti-inflammatory and anti-allergic effects that are promoted by inhibiting cytokine release, infiltration of inflammatory cells, and airway remodeling in animal models [22,23]. The safety of SCRT has been demonstrated in previous clinical trials and in vivo studies [24,25]. Considering its efficacy and safety, SCRT was selected as the investigational medicine in this study.

This study aims to investigate the efficacy, safety, and economic evaluation of WBGCT for UACS-induced chronic cough, a feasibility study to demonstrate its possibilities, including the duration of intervention, recruitment of participants, outcome measures, and effect size before this trial.

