#### 2.3.2. Control Group

Participants in the control group will be instructed to take three packs of active comparator (SCRT) before or between meals three times per day for 2 weeks. SCRT consists of eight medicinal herbs: Ephedrae Herba 0.3 g, Paeoniae Radix 0.51 g, Pinelliae Tuber 0.47 g, Schisandrae Fructus 0.55 g, Cinnamomi Ramulus 0.04 g, Asiasari Radix et Rhizoma 0.18 g, Glycyrrhizae Radix et Rhizoma 0.34 g, and Zingiberis Rhizoma 0.28 g, which is manufactured as brown granules. SCRT will be purchased from the Kyungbang Pharm Corporation. The ingredients and compositions of the WBGCT and SCRT are listed in Table 2.

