### 2.7. Assignment of Interventions

#### 2.7.1. Allocation

The participants are allocated according to blocked randomization without stratification. A randomized allocation sequence will be assigned to each group based on a computer-generated random number table created by an independent statistician using SAS version 9.4 statistical software (SAS Institute. Inc., Cary, NC, USA). After consent to the clinical trial, the participants’ identification code will be assigned to those who meet the inclusion and exclusion criteria. The participants will be allocated to the WBGCT and control groups at an allocation ratio of 1:1. The randomization table will be retained separately by the independent statistician to maintain blinding. The assignment of participants will be conducted according to the assignment table generated by a random assignment method that can be specifically planned and reproduced in advance. According to the randomized assignment table, the participants’ identification codes will be kept in an opaque envelope and a cabinet with double locks.

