## 5. Conclusions

This study aims to demonstrate the effects of WBGCT on UACS-induced chronic cough. As WBGCT has been used widely for respiratory diseases over a long period of time with few side effects, WBGCT is expected to be a safe and effective agent for UACS-induced chronic cough. Moreover, considering that our intervention is Korean medicine, we used pattern identification to obtain additional information on whether certain patterns of patients respond better than others to the treatment. Additionally, we perform an economic evaluation of WBGCT compared to SCRT, expecting the expansion of newly applied health insurance-covered herbal formulas. Our study will support the efficacy, safety, and economic feasibility of WBGCT and provide evidence for its clinical use.

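### Section 5 says in advance that the study will support WBGCT's safety, but the only between-arm safety analysis stated is a Fisher's exact test in at most 15 dosed participants per arm, which cannot do that

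*Protocol article*

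**What the plan says.** Safety is one of the three stated aims. The Introduction gives a specific reason for it: "since the adverse effects of WBGCT including palpitation and insomnia have been reported [19], we will assess the safety of WBGCT".

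Section 2.9 defines the safety population: "A safety evaluation will be conducted on participants who receive Interventions at least once". It then gives the AE analysis: "The number of AEs between the groups will be compared using Fisher’s exact test". Laboratory values get a before-and-after paired test. No analysis is stated for vital signs. Section 2.5 also lists the electrocardiogram, but Table 1 schedules it only at visit 1.

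On size, Section 2.2.2 starts from a pilot-study rule of 12 per group and adds an allowance: "Considering a 20% dropout rate, 30 participants (15 per group) will be recruited". Section 2.7.1 sets 1:1 allocation. No AE rate, safety margin, significance level or safety power appears.

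Section 5 closes with: "Our study will support the efficacy, safety, and economic feasibility of WBGCT and provide evidence for its clinical use".

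**The concern.** The article names a test of difference for AEs and, separately, states before any data exist that the study will support safety. These do not fit together. In arms this small, a difference test will usually be non-significant whether or not WBGCT causes more adverse events than SCRT. A non-significant p-value therefore says little about safety, and the article states no other between-arm criterion, such as a margin or a bound on an event rate, that could bear the claim.

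At stake is how the final report is read. If the Section 5 sentence is carried over and the AE comparison is non-significant, readers could take the two together as evidence of safety, although the data would still be compatible with a large excess of events, including the palpitation and insomnia that the Introduction names.

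**Working it through.** **Inputs from the protocol article**
- 12 per group before dropout, 20% dropout, 15 per group recruited (Section 2.2.2).
- 1:1 allocation (Section 2.7.1).
- Safety population: everyone dosed at least once (Section 2.9). A participant who drops out after the first dose stays in, so the relevant size is up to 15 per arm, not 12.

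**Assumptions made here, because the article gives none**
- Two-sided 5% significance level.
- Participants with at least one AE are counted.
- AE rates as shown below.

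**Step 1. The plan's own figure.** 12 / (1 − 0.20) = 15 per group, and 2 × 15 = 30. This reproduces.

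**Step 2. Power of Fisher's exact test at 15 per arm.** All 2×2 tables with 15 per row were enumerated. Power is the sum of Bin(x; 15, p₁) × Bin(y; 15, p₂) over tables with p ≤ 0.05.

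| Assumed AE rates | Power | Missed |
|---|---|---|
| 5% v 15% | 3.0% | 97.0% |
| 10% v 30% | 14.9% | 85.1% |
| 10% v 40% | 32.5% | 67.5% |
| 10% v 50% | 53.6% | 46.4% |
| 20% v 60% | 44.7% | 55.3% |

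A one-sided 5% test for 10% v 30% has 25.6% power and still misses 74.4%.

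**Step 3. Results that need no assumed rate (15 per arm).**
- Four affected v none: p = 2 × C(15,4)/C(30,4) = 2 × 1365/27405 = 0.10.
- Five affected v none: p = 2 × C(15,5)/C(30,5) = 2 × 3003/142506 = 0.042. So five v none is the smallest split against zero that reaches p ≤ 0.05.
- With one event on the other arm, seven are needed.
- Zero events in 15: the one-sided 95% upper bound is 1 − 0.05^(1/15) = 0.181. The upper limit of the two-sided 95% interval is 1 − 0.025^(1/15) = 0.218.

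**Step 4. What estimation would show instead.** Take five of 15 on WBGCT and one of 15 on SCRT. Fisher's test gives p = 0.17. The risk difference is 5/15 − 1/15 = 26.7 percentage points, with a Newcombe 95% CI of about −3 to +52 points. The p-value alone would be reported as no significant difference; the interval shows that a large excess is not excluded.

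**The case against.** The case on the other side is substantial.

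- **The trial is exploratory and says so.** It uses a pilot rule for its size, and Section 4 lists small size, short duration and the lack of a placebo arm as limitations. Low power for AEs is normal in such a trial. This stands, and the sample size is not criticised here. But the small-size limitation is discussed in terms of feasibility and of sizing a later efficacy trial; it does not qualify the safety sentence in Section 5.
- **Fisher's exact test is valid for sparse counts, and an article may leave intervals to the full protocol or analysis plan.** This also stands. The absence of an interval would be no finding alone. The problem is the pairing of this analysis with an advance claim that it cannot support, and an unseen analysis plan would not correct that sentence.
- **Safety draws on more than AEs.** Correct: a reader might infer that the whole safety assessment rests on one test, and the documents do not support that. Vital signs and laboratory tests are assessed too. However, the laboratory tests compare before with after, no between-arm analysis is stated for either, and the electrocardiogram is scheduled only at screening.
- **No decision rule is stated.** A reader might infer that the sponsor plans to treat a non-significant p-value as proof of safety. Nothing in the article says so. Section 5 also contains a separate expectation of safety, which is attributed to long prior use and not to this test.
- **The comparator.** SCRT also contains ephedra ("SCRT consists of eight medicinal herbs: Ephedrae Herba 0.3 g"), so a reader might infer that the trial compares two similar ephedra products. The listed amounts do not support that: Section 2.3.1 and Table 2 give 3.75 g for WBGCT, and 3.75 / 0.3 = 12.5. The point made here does not depend on the comparator's composition.

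**Conclusion.** The concern holds in a limited form. The single between-arm safety analysis stated, in at most 15 dosed participants per arm, cannot support the safety statement that Section 5 makes in advance.

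The miss rate of about 85% is conditional on assumed rates of 10% and 30% and a two-sided 5% level. Another tripling, 20% to 60%, is missed about 55% of the time, so no single figure should be quoted without its assumptions. The five-against-none threshold depends only on the assumed level, and the 18% one-sided bound (22% as a two-sided limit) only on the number dosed. Fewer than 15 dosed per arm would raise the bound.

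The severity is minor. The defect lies in the wording of the conclusion and in using a difference test where estimates are needed, not in the design, the sample size or the validity of Fisher's test.

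**What to change.** In Section 2.9, make estimation the basis of the safety summary:
- Report by arm the number and percentage of participants with at least one AE, and separately with palpitation and with insomnia.
- Give the WBGCT-minus-SCRT risk difference with a 95% CI (for example Newcombe), and the exact upper 95% bound on each WBGCT rate.
- Keep Fisher's exact test, if wanted, as a descriptive addition.
- State that a non-significant difference will not be taken as evidence of safety.

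In Section 5, replace the claim about supporting safety with wording such as: *will give preliminary estimates of adverse event rates*.

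The data are already to be collected, so this needs no extra participants, visits or measurements. It costs a few sentences and a less favourable safety claim.
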